### Participants and recruitment

#### Eligibility criteria

The target study population is treatment-seeking adults with moderate to severe CUD under conditions of informed consent. Eligibility will be assessed by an Addiction Medicine or Psychiatry credentialed Study Medical Officer (SMO).

Inclusion criteria*:*Aged 18 to 65 years.Meeting DSM-5 criteria for moderate or severe CUD (≥ 4/11 criteria) [2], with recent frequent cannabis use (≥ 4 days per week in the preceding 4 weeks).Willing and able to provide informed consent to study procedures.Proficient in English at a conversational level sufficient to participate in a counselling intervention.

*Exclusion criteria* aim to exclude individuals with conditions that jeopardise safety or confound data interpretation:Prescribed medicinal cannabis products (e.g., CBD, THC) for any indication in the previous 4 weeks.Another active (past year) moderate-severe substance use disorder other than tobacco; determined on clinical assessment using DSM-5 criteria.Active or severe medical (e.g., pain, epilepsy, cardiovascular disease) or psychiatric (e.g., psychosis, severe affective disorder) conditions based on clinical assessment.Moderate to severe hepatic disease (transaminase elevations > 3 times, bilirubin > 2 times upper normal limits at screening).Pregnant or lactating women (based on urine β-hCG at screening).Hypersensitivity to CBD or any excipients of Investigational Product.Using medications with known drug-drug hepatic CYP-450 interactions with CBD: 3A4, (e.g., carbamazepine, fluvoxamine, methadone), 2C19 (e.g., rifampin); CYP2B6 (e.g., bupropion), CYP2C9 (e.g., warfarin).Not available during treatment or follow-up (e.g., travel, impending residential detoxification or residential rehabilitation admission, impending imprisonment).Court-mandated treatment requiring abstinence from drugs.Current active (counselling and/or medication-based) treatment for CUD.Received an investigational medicinal product within the last 4 weeks (or 5 half-lives if using long-acting investigational drugs).

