#### Participant numbers

Sample size calculations are based on the analysis of the primary outcome, that is, the difference between placebo and CBD groups in total number of Cannabis-free Days over the 12-week intervention period. Ferguson has suggested that the minimum effect size (Cohen’s *d*) for an effect of practical clinical significance is 0.4167 [55]. To achieve 90% power (two-tailed) and α = 0.05, a total of *N* = 250 (*n* = 125 per group) participants are needed to detect a between-group effect size of *d* = 0.41. Of the target 250 sample, it is estimated approximately 20% (*n* = 50) of the study sample (*N* = 250) will be Indigenous Australians.

Participants who discontinue study procedures after commencing study interventions (medication dispensed on Day 1) will not be replaced in the study but will be included in the modified intention-to-treat analyses. Participants enrolled and randomised, but do not commence any treatment (no medication dispensed or other clinical interventions) will not be included in the final analysis.

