### Outcome measures

The *primary outcomes* are illicit cannabis use during the 12-week intervention period, operationalised using two endpoints:*Cannabis-free Days* over the 12-week intervention period, producing a continuous measure between days 1 and 85. Details regarding number of days of cannabis use will be collected at each research interview (baseline week 1, weeks 4, 7, 10, week 13 and 25) using the Time Line Follow Back (TLFB) approach, a reliable and validated measure of cannabis use, particularly when combined with biological assays (e.g. UDS) and confidentially reported to independent researchers^74^.*Urinary quantitative analysis of THC-COOH (creatinine adjusted)*. Urine samples will be collected at weeks 1, 4, 7, 10, 13 and 25, and analysed using liquid chromatography-tandem mass spectrometry (LCMS). As THC-COOH can remain ‘positive’ using qualitative thresholds (e.g. 20 ng/ml in LCMS assays) for more than 30 days after abstinence in chronic heavy cannabis users [58], we will analyse quantitative levels of THC-COOH (creatinine adjusted) to detect differences in cannabis use between the two study groups, replicating the approach used in the pilot RCT [29] (see below).

Secondary outcomes (Table 1) include a range of measures that relate to cannabis use (including rates of abstinence or reduced frequency of cannabis use, cannabis withdrawal and cravings, cannabis related problems, severity of CUD), safety (adverse events), health outcomes (including mental health, physical health, QoL), consumer experience of the medication, cognitive performance, other substance use and post-treatment outcomes (12 weeks after the intervention). The relationship between experiences of racial discrimination (using the modified Everyday Discrimination Scale) and outcomes for Indigenous Australians will also be explored.

**Table 1 Tab1:** Table of all primary and secondary outcome measures included in study

Domain	Name	Description of measure	Administration timepoint
**Basic**	Demographics	7 Questions: basic demographics including: age, gender, sexuality, Aboriginal and Torres Strait Islander background, education level, employment status, relationship status and living situation. Categorical data, excluding age which is discrete numeric	Research Interview: Week 1 (baseline) Day 1

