**RESEARCH ASSESSMENTS**							
Research Interviews^d^: Collection of UDS, TLFB, Quantity of Cannabis Use, SUG, Rates of Abstinence, PROMIS-29, Testing of the Blind, CWS, MCQ, ATOP, FTND		X	X	X	X	X	X
DSM-5, PTSD, MPQ		X				X	X
TSQM, DEQ-5			X	X	X	X	X
PSIa		X		X		X	X
Treatment Retention						X	
Cognitive assessments^e^: RAVLT, NART-17, Eriksen Arrow Flankers Task, N-Back, Digit Span Task, TMT		X				X	
Interviews with Indigenous Australian participants + m-EDS^f^		X		X			

^a^Medical screening to be conducted within 4 weeks of study enrolment on Week 1, Day 1

^b^Adverse event assessments and concomitant medications are assessed by the study medical officer or clinical nurse specialist

^c^Cognitive behavioural therapy intervention to be conducted by experienced cannabis counsellors. Three sessions to be conducted over the first 6 weeks of treatment and one session between weeks 7–13 of intervention period

^d^All research interviews and cognitive assessments will be conducted by the site coordinator. See Table 1 for descriptions of each research measure

^e^RAVLT: This task assesses verbal learning and memory; NART-17 = National Adult Reading Test: this task assesses pre-morbid IQ; Eriksen Arrow Flankers Flankers: This test assesses both choice reaction time and the ability to ignore distracting but irrelevant information; N-back: this is a working memory task; Digit span task: evaluates working memory; Trail Making Test: assesses attention, processing speed, and cognitive flexibility

^f^Modified Everyday Discrimination Scale (m-EDS) will be conducted at Week 1 baseline and a qualitative research interview with consenting Indigenous Australians will be conducted by the study’s Aboriginal Research Coordinator between weeks 7–13

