#### Primary outcomes

We will model the effects of CBD on number of cannabis free days (out of 84 days) via single-level Gaussian regression with the outcome regressed on the main covariate experimental group (placebo vs CBD). Number of cannabis-free days in the 28 days prior to baseline will be included as a covariate to control for variation in participants’ prior frequency of use entering the study. Two treatment factors that could plausibly influence the primary outcomes and which vary across participants will also be included as covariates: number of counselling sessions attended during the study period (count variable range 0–4), and whether or not NRT was taken (binary variable measured at baseline: did not undertake NRT vs undertook NRT). If residuals are distributed normally, we will report the results from this analysis. If residuals are not distributed normally, we will treat cannabis-free days/84 as a bounded count instead of a numeric variable and use aggregated binomial regression with a logit link.

We will model urinary THC-COOH levels (a continuous outcome, in ng/MoL) via random-slopes mixed-effects models with the group, time (6-level categorical ordered predictor; Weeks 1 (baseline), 4, 7, 10, 13), the group × time interaction, number of counselling sessions attended, and whether or not NRT was undertaken as the fixed factors, and participant ID as the random factor.

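### The cannabis-free-days model has one baseline measure of cannabis use, a day count that eligibility narrows, and leaves out the Week 1 THC-COOH already collected: a missed efficiency, not an error

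*Protocol article*

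**What the plan says.** Under Data analysis, Primary outcomes, the protocol article models "number of cannabis free days (out of 84 days) via single-level Gaussian regression", with treatment group as the main term. It then states: "Number of cannabis-free days in the 28 days prior to baseline will be included as a covariate". Two further covariates are named: "number of counselling sessions attended during the study period (count variable range 0–4), and whether or not NRT was taken". The article describes NRT as a binary variable measured at baseline. If the residuals are not normal, the analysis moves to aggregated binomial regression with a logit link.

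The entry rule, under Eligibility criteria, is moderate or severe cannabis use disorder with "recent frequent cannabis use (≥ 4 days per week in the preceding 4 weeks"). Footnote a to Table 2 adds: "Medical screening to be conducted within 4 weeks of study enrolment on Week 1, Day 1".

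Under Outcome measures, for the second primary endpoint: "Urine samples will be collected at weeks 1, 4, 7, 10, 13 and 25". These are assayed for quantitative, creatinine-adjusted THC-COOH. The use that the Primary outcomes section gives to the Week 1 value is as the baseline level of time in the THC-COOH mixed model. It does not appear in the cannabis-free-days model.

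**The concern.** A baseline covariate improves precision only to the extent that it separates participants who will do differently on the outcome. Here the entry rule removes the lighter users, so the day count has little room to vary. Among daily users it does not vary at all: someone who uses a little every day and someone who uses heavily every day both score zero free days. Quantitative THC-COOH could still grade exposure within that group, and the trial already treats it as a measure of the same construct.

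The other two covariates do not fill the gap. Counselling attendance is counted after randomisation, and NRT concerns nicotine. Randomisation is stratified by site and Indigenous status, not by heaviness of use.

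What is at stake is the width of the interval around the CBD effect on one of the two primary endpoints, at the price of one added term and no new data collection.

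**Working it through.** **Inputs from the protocol article.** d = 0.41, 125 per arm, two-sided α = 0.05, 90% power (Participant numbers); use on at least 4 days a week for 4 weeks (Eligibility criteria); a 28-day baseline count (Primary outcomes). The documents give no correlation between baseline THC-COOH and the outcome.

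**1. The plan's own figure.** The article states its target as "To achieve 90% power (two-tailed) and α = 0.05, a total of *N* = 250 (*n* = 125 per group) participants are needed"; the standardised difference behind it is 0.41. With the normal approximation:

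- n per arm = 2(1.960 + 1.282)² / 0.41² = 125.01, which rounds up to 126 (252 in total).
- Power at 125 per arm = Φ(0.41 × √(125/2) − 1.960) = Φ(3.241 − 1.960) = 0.900. The t-test version gives 0.898.

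The stated figure reproduces, and it takes no credit for any covariate.

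**2. Range of the day count.** Minimum use days = 4 × 4 = 16. Maximum free days = 28 − 16 = 12. The count therefore runs over about 0 to 12 of 28. The limit is approximate, because screening may precede Week 1 by up to 4 weeks and the 28 days before baseline need not be the window that was screened.

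**3. What narrowing can do (illustration only).** If values were spread evenly, the SD would be √((13² − 1)/12) = 3.7 on 0–12, against √((29² − 1)/12) = 8.4 on 0–28, a ratio u of 0.45. An assumed unrestricted correlation ρ of 0.5 with the outcome would fall to ρu / √(1 + ρ²(u² − 1)) ≈ 0.25, an R² of about 0.06. The documents give no baseline distribution, so this shows direction only.

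**4. Possible gain from Week 1 THC-COOH.** Let R² be the share of the residual variance, after the existing covariates, that log Week 1 THC-COOH explains (assumed). The residual SD is multiplied by √(1 − R²), and power = Φ(3.241/√(1 − R²) − 1.960). Equivalent N = 250/(1 − R²).

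| Assumed incremental partial R² | Interval narrower by | Power, no credit for the day count | Equivalent N |
|---|---|---|---|
| 0 | 0% | 0.900 | 250 |
| 0.01 | 0.5% | 0.903 | 253 |
| 0.05 | 2.5% | 0.914 | 263 |
| 0.10 | 5.1% | 0.927 | 278 |
| 0.16 | 8.3% | 0.943 | 298 |

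The t-test version of the last row is 0.941.

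**5. Starting power.** Step 4 starts from the unadjusted 0.900, although the planned model already contains the day count. If the day count explained 6% of outcome variance (the illustration in step 3), starting power would be Φ(3.241/√0.94 − 1.960) = 0.917. Adding R² = 0.16 would then give Φ(3.241/√(0.94 × 0.84) − 1.960) = 0.954. The increment is 3.8 points instead of 4.3. The power increments in the table are therefore upper readings for each R²; the narrowing of the interval is unaffected.

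**The case against.** The strongest reply is that nothing here is wrong. The model adjusts for the baseline version of its own outcome, which is a standard choice with a stated reason, and the sample size relies on no covariate. That stands.

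A reader might infer that the trial is underpowered without THC-COOH, or that the model adjusts for the day count and nothing else. The documents support neither. The 90% power reproduces unadjusted, and counselling sessions and NRT are also in the model. Nor can one say that the count is piled up at zero: the share of daily users is not given, and 0 to 12 is not a strict bound.

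Other Week 1 measures, such as the DSM-5 criteria count, withdrawal and craving, could be proposed on similar grounds, and no evidence in the documents ranks THC-COOH first. That is fair. The reason to prefer it is that the protocol itself makes it the other primary measure of cannabis use. Its added value beyond the day count could still be nil.

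Chance imbalance in heaviness of use is not a validity problem, since the interval already allows for it. That stands too.

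The precision argument belongs to the Gaussian model. Under the logit fallback, adding a covariate also changes the conditional odds ratio being estimated, so the gains above do not carry over directly.

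These points narrow the claim, but none shows harm from the change. In the Gaussian model a pre-dose covariate does not bias the randomised comparison, and an uninformative one costs one coefficient in 250 participants.

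**Conclusion.** The point holds as a missed efficiency. The cannabis-free-days model has a single baseline measure of cannabis use, one that eligibility narrows to roughly 0 to 12 of 28 days and that cannot distinguish among daily users. A quantitative measure of the same construct, collected at Week 1, is left out.

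The size is not known. For an assumed incremental partial R² between 0 and 0.16, power at d = 0.41 and 125 per arm lies between about 90% and about 94%, an increment of 0 to about 4 points, and less if the day count already raises the starting power. This rests on the Gaussian model, complete data and a Week 1 sample taken before the first dose. The planned power does not depend on the change.

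**What to change.** In Data analysis, Primary outcomes, before unblinding, add log Week 1 creatinine-adjusted THC-COOH as a fixed baseline covariate in the cannabis-free-days model, beside the 28-day count of cannabis-free days. State that the Week 1 sample is taken before the first dose, and that missing Week 1 values go into the planned multiple imputation. Say also whether the covariate is kept under the binomial fallback, and note that the odds ratio there is conditional on it.

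The cost is a sentence or two of wording, one more coefficient, and imputation of any missing Week 1 urines. No new data are collected.

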#### Informed consent, randomisation and blinding

Written informed consent is obtained on Week 1, Day 1 of the study prior to the commencement of all subsequent study procedures. Consent is obtained with the site coordinator independent of treating clinicians, to minimise ‘pressure’ to participate in the study.

The randomisation schedule has been developed by an independent statistician, with eligible participants randomised in a 1:1 ratio between groups using variable block randomisation to help maintain blinding, with subjects stratified by (a) site (to achieve approximately equal numbers of active and placebo at each site) and (b) Indigenous Australian status (to allow direct between-group statistical comparisons within Indigenous Australian participants).

Participants, clinicians, and researchers involved in service delivery, data collection and analysis will remain blinded to study conditions using matched placebos manufactured by the same manufacturer. CBD and placebo will be packaged in identically labelled containers with the participant’s ID number and site. Aside from site trial pharmacists (who have no direct contact with participants), all other members of the clinical or research teams will be blinded to group allocation.

Unblinding will occur after all data are collected, entered, cleaned and the trial database has been locked. In circumstances where allocation needs to be unblinded (e.g. severe adverse event), the principal investigator will authorise the local site investigator to break the blind (via the site trial pharmacist).

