### Interventions

#### Medications

The experimental condition will receive 12 weeks of CBD oral 400 mg daily, administered as 200 mg liquid administered twice a day (BD). The CBD used in the trial is a plant-extracted pharmaceutical product (registered in Australia as Epidyolex® for the treatment of paediatric epilepsy), and is an oral liquid (clear, colourless to yellow solution) containing 100 mg per ml, dispensed in 105 ml bottles. The placebo is identical in composition and appearance (with the exception of the CBD). Both CBD and placebo are manufactured and supplied by Jazz Pharmaceuticals.

The dose is selected based on the findings of the Phase IIa RCT [29] that identified a daily dose of 400 mg CBD being more efficacious than placebo at reducing cannabis use during 4-week treatment and follow up.

Nicotine dependent participants will be offered smoking cessation counselling during the trial, with prescriptions and supply of nicotine replacement therapy (NRT) either in the form of 16-h topical patches (7, 14 or 21 mg) and/or nicotine chewing gum or lozenges provided.

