#### Secondary outcomes

All repeated measures of secondary outcomes will be modelled using the same approach as for urinary THC-COOH. That is, random slopes mixed-effects models for repeated measures regressions with group, time, the group × time interaction, number of counselling sessions attended, and whether or not NRT was taken as the fixed factors. These models will all be based on the generalised linear model, with link functions differing depending on the form of the outcome, as follows:Numeric (e.g., PROMIS-29 scores, marijuana craving questionnaire scores): Gaussian regression with identity link functionOrdinal (e.g., motivation to change cannabis use): ordinal logistic regression with logit link functionBounded count (e.g., severity of CUD) or binary (e.g., participant rating of group allocation): binomial logistic regression with logit link functionUnbounded count (e.g., adverse event count): negative binomial regression with log link function

See Table 1 for the form of each outcome measure.

Several secondary outcomes are single observations per individual. Group, number of counselling sessions attended, and whether or not NRT was taken will be the sole predictors in these models. Total abstinence from cannabis during weeks 10–13 (non-abstinent vs abstinent) and 50% increase in cannabis-free days during weeks 10–13 relative to cannabis-free days prior to baseline (< 50% reduction vs ≥ 50% reduction) will be modelled with binary logistic regression with logit link function, relative risk of adverse events during the trial period with negative binomial regression with log link function, hazard of treatment dropout via discrete-time hazard model with complementary log–log link function.

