#### Statistical methods for Indigenous Australian focussed outcomes

Indigenous Australian and non-Indigenous participants will be compared on baseline participant characteristics (e.g., age, gender, frequency of substance use, scores on quality-of-life scales) via simple regression: Gaussian for continuous measures, Logistic for binary and count variables, and multinomial logistic for multilevel categorical data. For the main study analyses, comparing the frequency of illicit cannabis use between placebo and CBD groups, all participants will be pooled and included in main analyses, irrespective of Indigenous status. However, an additional regression will be performed where Indigenous status and the interaction between Indigenous status and the study drug (Placebo vs CBD), along with the primary predictor study drug, will be included in the regression.

The study will stratify randomisation according to Indigenous status, to achieve an approximately equal number of Indigenous Australian participants on active and placebo conditions, thus requiring no additional statistical procedures beyond those outlined in the previous paragraph.

The effect of the experience of discrimination on outcomes related to cannabis use disorder will be estimated via regressing various outcomes related to cannabis use on scores on the modified Everyday Discrimination Scale (m-EDS). Two regressions will be performed for each outcome, with a different version of the m-EDS as the primary predictor in each: (i) a continuous version of the scale (i.e., total score) and (ii) a three-level categorical version of the scale (no vs low vs moderate-to-high). The outcomes that the m-EDS will be regressed on will be: (i) (baseline characteristics (e.g., years of regular cannabis use, scores on quality-of-life scales), (ii), treatment engagement (e.g., treatment retention, number of counselling sessions) and (iii) outcomes during the trial (e.g., frequency of cannabis use, health measures). As described above, the type of regression will depend on the type of outcome: Gaussian for continuous, logistic for binary or bounded count, ordinal logistic for ordered categorical, and negative binomial for unbounded count. The effect of m-EDS on treatment retention will be estimated via Kaplan Meier plots discrete-time hazard model with complementary log–log link function.

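### Adjusting for counselling sessions attended, a post-randomisation variable, can bias the CBD effect on cannabis-free days and distorts the dropout model; the timing of the NRT covariate is contradictory

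*Protocol article*

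**What the plan says.** Under Data analysis, Primary outcomes, the protocol article regresses cannabis-free days out of 84 on group, cannabis-free days in the 28 days before baseline, "number of counselling sessions attended during the study period" (0 to 4), and NRT, described as a "binary variable measured at baseline: did not undertake NRT vs undertook NRT". The urinary THC-COOH model carries sessions and NRT as fixed factors beside group, time and group × time.

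Under Secondary outcomes, the repeated measures follow the THC-COOH model. For outcomes observed once per person (total abstinence, 50% response, adverse events, dropout hazard), "Group, number of counselling sessions attended, and whether or not NRT was taken will be the sole predictors in these models".

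Three other places bear on timing:

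- Counselling (under Interventions) places the sessions in the 12-week medication phase, after randomisation in Week 1.
- Statistical methods for Indigenous Australian focussed outcomes lists "treatment engagement (e.g., treatment retention, number of counselling sessions" among the outcomes to be regressed on the discrimination scale.
- Medications says "Nicotine dependent participants will be offered smoking cessation counselling during the trial", with NRT prescribed and supplied.

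No efficacy model without the sessions covariate is described.

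**The concern.** The article declares a modified intention-to-treat analysis, and its primary aim concerns CBD used in combination with psychological interventions. Both call for the total effect of allocation. Attendance is observed after allocation, and CBD could change it through craving, withdrawal, adverse effects or retention. It also plausibly shares causes with cannabis use, motivation above all.

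Holding it fixed does two things. It removes any benefit that works through better engagement. It also compares people who reached the same attendance for different reasons, which opens a non-randomised path through motivation. A larger sample does not cure this, and neither does a Bayesian model.

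At stake are the interpretation of one of the two primary endpoints and of the single-observation secondary outcomes. For dropout there is a further problem: the predictor is partly determined by the event being modelled.

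**Working it through.** **1. The plan's own figure.** Inputs from Participant numbers and from the randomisation section: "To achieve 90% power (two-tailed) and α = 0.05", N = 250 "participants are needed to detect a between-group effect size of *d* = 0.41", with "eligible participants randomised in a 1:1 ratio between groups".

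n per arm = 2(z₀.₉₇₅ + z₀.₉₀)² / d² = 2(1.960 + 1.282)² / 0.41² = 21.02 / 0.1681 ≈ 125.05, so 126 per arm (252 in total). Power at 125 per arm is 0.900 (0.898 by the noncentral t). The stated 250 reproduces. It is an unadjusted two-group comparison, so it does not depend on the sessions covariate.

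**2. Cannabis-free-days model.** In a linear model with group and sessions,

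adjusted group coefficient = total difference − b × (between-arm difference in attendance),

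where b is the within-arm slope of outcome on attendance. Bias needs both b and the attendance difference to be non-zero.

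The inputs below are assumptions; the documents give none of them. Latent attendance and outcome each have SD 1 within arm, and sessions have no causal effect.

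- Correlation 0.4 through motivation: b = 0.4.
- The same, plus a baseline covariate with loading √0.5 on motivation: b = (0.4 × 0.5) / (1 − 0.4 × 0.5) = 0.2 / 0.8 = 0.25.
- Correlation 0.25 (loading 0.5 on each), no baseline covariate: b = 0.25.

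The simulations used 250 participants and a 0–4 session count. The arithmetic treats attendance as continuous and so shows slightly more bias.

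| CBD effect on attendance (SD) | 0.41 − 0.4a | Simulated, correlation 0.4 | 0.41 − 0.25a | Simulated, correlation 0.4 with baseline | Simulated, correlation 0.25 |
|---|---|---|---|---|---|
| 0 | 0.41 | not shown | 0.41 | not shown | 0.41 |
| +0.2 | 0.33 | 0.34 | 0.36 | 0.37 | 0.37 |
| +0.4 | 0.25 | 0.27 | 0.31 | 0.32 | 0.32 to 0.34 (two runs) |
| −0.3 | 0.53 | 0.52 | 0.485 | not shown | 0.48 |

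If sessions do help (0.15 SD each) and CBD raises attendance by 0.4 SD, then in the correlation-0.25 simulation a total effect of 0.475 is estimated as 0.34. The part that works through engagement is lost.

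**3. Repeated-measures models.** Sessions enter as a time-constant main effect, with no sessions × time term. Write ȳ for the mean in arm g at visit t, s̄ for mean sessions in the arm and γ for the sessions coefficient. With an identity link and complete data:

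- Group difference at visit t: (ȳ₁ₜ − ȳ₀ₜ) − γ(s̄₁ − s̄₀). The covariate matters.
- Group difference in change from baseline: (ȳ₁ₜ − ȳ₁,base) − (ȳ₀ₜ − ȳ₀,base). The γ terms cancel.

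A simulation with 250 participants and 5 visits agreed to three decimals with and without sessions, for random-intercept and random-slope structures. The cancellation is not established for logit or log links.

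**4. Dropout model.** A footnote to the schedule (Table 2) places three sessions in the first 6 weeks and one in weeks 7–13. If that is followed and counselling stops at dropout, someone who leaves in the first 6 weeks can have at most three sessions, and anyone with four was still in treatment after week 6. Among participants with four sessions, early dropout is then impossible by construction. The total count carries later information into the earlier hazard.

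**5. NRT.** Primary outcomes says it is measured at baseline. The same section calls it a treatment factor and asks whether it was taken. Medications describes supply during the trial, and Secondary outcomes again says taken. These descriptions cannot all define one variable.

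**The case against.** The plan has a case. Counselling exposure varies, it predicts outcome, and adjusting for it reduces residual variance. The trial is blinded, and nothing in the documents shows that CBD alters attendance. The baseline covariate absorbs part of the shared motivation. All of this limits the likely size of the bias. It does not restore the intention-to-treat effect if attendance does respond, and that cannot be known when the model is fixed.

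Four stronger readings are tempting, and the documents do not support them:

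- *Both covariates are post-randomisation.* NRT carries a baseline label. What can be shown is a conflict over its timing.
- *Every model is biased.* Step 3 shows that the change-from-baseline contrast escapes in identity-link models with complete data. That covers THC-COOH if its effect is read as group × time. The article does plan imputation, so complete data is a condition and not a given.
- *False claims of efficacy are inflated to 9–23%.* Those are two-sided rejection rates under no effect, with attendance raised by 0.2 to 0.4 SD and correlation 0.4. Nearly all of them favour placebo: rejections favouring CBD fall to 0.5–0.1%, below the nominal 2.5%. With the baseline covariate the two-sided range is 7–12%. A spurious benefit needs CBD to lower attendance (at −0.3 SD and correlation 0.25: +0.06, rejection 7.6%). The article plans Bayesian models and states no rejection rule, so none of these rates is the plan's operating characteristic.
- *The dropout result is uninterpretable.* One rough illustration moved the hazard ratio only from 0.61 to 0.65. Distorted is the right word.

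**Conclusion.** The point holds for the cannabis-free-days primary model and the single-observation secondary models. They condition on a variable that follows randomisation and that the article itself treats as an outcome. The group coefficient then estimates the modified intention-to-treat effect only if CBD leaves attendance unchanged.

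The size is conditional. Against a true 0.41, the illustrations run from 0.27 (attendance raised by 0.4 SD, correlation 0.4) to 0.52 (lowered by 0.3 SD, correlation 0.4), with smaller errors under weaker shared motivation or when the baseline covariate carries part of it. The error is zero if attendance is unaffected. The documents fix neither size nor direction.

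The dropout model's defect is structural. In the repeated-measures models the concern is confined to group differences at a visit and to non-identity links. For NRT the finding is an internal contradiction to be reconciled. Because a primary endpoint is involved, the correction should be made before unblinding.

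**What to change.** Remove sessions attended from all efficacy, safety and dropout models, including the repeated-measures ones, so that no result depends on which contrast is read. Keep baseline cannabis-free days. Report attendance by arm as an outcome, and confine any session-adjusted model to an analysis labelled exploratory.

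Reconcile Medications, Primary outcomes and Secondary outcomes on NRT. Define the covariate strictly as status before randomisation, replace it with the baseline nicotine dependence score (FTND, already collected at Week 1), or drop it. If uptake during the trial is of interest, report it by arm.

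The cost is a change of wording and some lost reduction in residual variance. The sample-size calculation stands.
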